# Comparing biparametric to multiparametric MRI in the diagnosis of clinically significant prostate cancer in biopsy-naive men (PRIME): a prospective, international, multicentre, non-inferiority within-patient, diagnostic yield trial protocol

**DOI:** 10.1136/bmjopen-2022-070280

**Published:** 2023-04-05

**Keywords:** Prostate disease, Magnetic resonance imaging, RADIOLOGY & IMAGING, Protocols & guidelines, Urological tumours

## Abstract

**Introduction:**

Prostate MRI is a well-established tool for the diagnostic work-up for men with suspected prostate cancer (PCa). Current recommendations advocate the use of multiparametric MRI (mpMRI), which is composed of three sequences: T2-weighted sequence (T2W), diffusion-weighted sequence (DWI) and dynamic contrast-enhanced sequence (DCE). Prior studies suggest that a biparametric MRI (bpMRI) approach, omitting the DCE sequences, may not compromise clinically significant cancer detection, though there are limitations to these studies, and it is not known how this may affect treatment eligibility. A bpMRI approach will reduce scanning time, may be more cost-effective and, at a population level, will allow more men to gain access to an MRI than an mpMRI approach.

**Methods:**

Prostate Imaging Using MRI±Contrast Enhancement (PRIME) is a prospective, international, multicentre, within-patient diagnostic yield trial assessing whether bpMRI is non-inferior to mpMRI in the diagnosis of clinically significant PCa. Patients will undergo the full mpMRI scan. Radiologists will be blinded to the DCE and will initially report the MRI using only the bpMRI (T2W and DWI) sequences. They will then be unblinded to the DCE sequence and will then re-report the MRI using the mpMRI sequences (T2W, DWI and DCE). Men with suspicious lesions on either bpMRI or mpMRI will undergo prostate biopsy. The main inclusion criteria are men with suspected PCa, with a serum PSA of ≤20 ng/mL and without prior prostate biopsy. The primary outcome is the proportion of men with clinically significant PCa detected (Gleason score ≥3+4 or Gleason grade group ≥2). A sample size of at least 500 patients is required. Key secondary outcomes include the proportion of clinically insignificant PCa detected and treatment decision.

**Ethics and dissemination:**

Ethical approval was obtained from the National Research Ethics Committee West Midlands, Nottingham (21/WM/0091). Results of this trial will be disseminated through peer-reviewed publications. Participants and relevant patient support groups will be informed about the results of the trial.

**Trial registration number:**

NCT04571840.

Strengths and limitations of this studyProstate Imaging Using MRI±Contrast Enhancement (PRIME) is a pragmatic, prospective, international, multicentre trial being carried out in a range of different healthcare settings.Its within-patient design allows patients to act as their own control, improving the efficiency and power of the trial compared with a randomised study.Its within-patient design allows the impact of the dynamic contrast-enhanced sequences (DWIs) on staging decisions and treatment eligibility to be made at an individual patient level.PRIME will be one of the first trials to carry out quality control in the performance of sites’ DWIs prior to their involvement in the trial.As both biparametric and multiparametric targeted biopsies are carried out in the same patient, it is possible for the performance of one technique to influence the other.

## Introduction

This protocol was written according to SPIRIT (Standard Protocol Items: Recommendations for Interventional Trials) guidelines.^1^ MRI is widely established as the gold standard diagnostic imaging modality for detecting clinically significant prostate cancer (PCa).^2^ The landmark PRECISION (Prostate Evaluation for Clinically Important Disease: Sampling Using Image Guidance or Not?) trial established the benefit of detecting clinically significant PCa using MRI and targeting biopsies based on MRI findings.^3^ The National Prostate Cancer Audit data from England showed that only 62% of patients undergo prostate MRI before biopsy, despite level 1 evidence to support the use of MRI.^2–4^

Current recommendations for the use of MRI for detection of PCa focus on the use of multiparametric MRI (mpMRI).^2 3^ mpMRI consists of three sequences: T2-weighted sequence (T2W), diffusion-weighted sequence (DWI) and dynamic contrast-enhanced sequence (DCE). On the DCE sequences, cancer-suspicious areas can demonstrate early wash-in, enhancement and rapid wash-out of contrast.^5–8^ The DCE sequences involve administering gadolinium contrast via an intravenous cannula. Therefore, it increases scanning time and healthcare costs compared with a biparametric MRI (bpMRI) approach where only T2W and DWI are used. While gadolinium is in widespread use, literature suggests it may accumulate in the basal ganglia, though its clinical relevance is not fully understood.^9 10^ In patients who are likely to get repeated scans over their lifetime, there may be no advantage of using the additional contrast if the bpMRI option is as good as the mpMRI option.

Removing the DCE sequences from the MRI protocol has been suggested as a potential avenue to improve the cost-effectiveness of using MRI in the diagnostic pathway for PCa,^11 12^ and the reduced scanning time required may improve the number of men with suspected PCa accessing an MRI scan. Using bpMRI has demonstrated similar detection rates of PCa as mpMRI, but current evidence is limited primarily to retrospective, single-centre studies.^12 13^ The few prospective studies have not been typically robustly designed to evaluate the role of DCE in PCa detection.^13 14^

The Prostate Imaging Using MRI±Contrast Enhancement (PRIME) trial aims to assess whether bpMRI is non-inferior to mpMRI in the detection of clinically significant PCa. PRIME may redefine the standard of care diagnostic test for men with suspicion of PCa and may allow many more patients who need access to an MRI to get one.

### Objectives

The primary objective is to compare the detection of clinically significant PCa (Gleason score ≥3+4 or Gleason grade group ≥2) using bpMRI±targeted biopsy with mpMRI±targeted biopsy.

Key secondary objectives are:

To compare the proportion of men who have clinically insignificant PCa (Gleason score 3+3 or Gleason grade group 1) detected for bpMRI versus mpMRI.To compare the proportion of men with non-suspicious MRIs for bpMRI versus mpMRI.To compare the proportion of men with indeterminately scored MRI as reported by bpMRI and mpMRI.To compare the proportion of men with MRIs of adequate standard for reporting for bpMRI versus mpMRI.To compare the diagnostic test performance for bpMRI versus mpMRI.To compare radiological staging for bpMRI versus mpMRI.To compare treatment eligibility decisions for bpMRI when compared with mpMRI.To compare diagnostic performance of bpMRI and mpMRI when using the Likert scoring system in comparison to the Prostate Imaging Reporting and Data System (PI-RADS) V.2.1 scoring system.To compare the cost effectiveness of bpMRI when compared with mpMRI.

### Trial design

The PRIME trial is designed as a prospective, multicentre, within-patient, diagnostic yield trial, assessing whether bpMRI is non-inferior to mpMRI for the diagnosis of clinically significant PCa in biopsy-naive men. A paired cohort design was chosen rather than a randomised trial design for the following reasons:

More efficient design (sevenfold lower sample size required) with equivalent quality of evidence in the setting of a diagnostic study.Patients act as their own control due to the within-patient design, thus allowing us to draw conclusions regarding the value of DCE sequences on a per patient level.Allows for the evaluation of the impact of contrast on staging decisions and treatment eligibility decisions at an individual patient level.Patients get the benefit of having targeted biopsies based on the information from both bpMRI and mpMRI information, whereas with a randomised study, patients randomised to one technique will be denied of potential benefit of the other.

## Methods and analysis

### Trial setting

We expect centres that perform PCa diagnostics and management from the following countries to take part: Argentina, Australia, Belgium, Brazil, Canada, Denmark, France, Finland, Germany, Italy, the Netherlands, Singapore, Spain, UK and USA. Sites will be required to undergo a period of quality control prior to including patients to ensure minimum acceptable standards for the conduct of mpMRI, reporting and targeted biopsy.

### Eligibility criteria

Patients will be considered eligible for registration into this trial if they fulfil all of the inclusion criteria and none of the exclusion criteria (box 1).

Box 1Eligibility criteriaInclusion criteria.Men at least 18 years of age referred with clinical suspicion of PCa.Serum prostate-specific antigen of ≤20 ng/mL.Fit to undergo all procedures listed in the protocol.Able to provide written informed consent.Exclusion criteria.Prior prostate biopsy.Prior treatment for PCa.Prior prostate MRI on a previous encounter.Contraindication to MRI (eg, claustrophobia, some pacemakers).Contraindication to prostate biopsy.Unfit to undergo any procedures listed in the protocol.PCa, prostate cancer.

### Interventions

#### MRI conduct

MRI will be conducted with 1.5 or 3.0 T with pelvic-phased array coils, with or without endorectal coils. The PRECISION study quality control highlighted that the image quality of the DCE sequences was the most variable sequence across sites.^3^ Therefore, to give DCE a reasonable chance of demonstrating whether it has value, MRI scanner approval for use in the study will be made on the basis of central review of MRI images, using the Prostate Imaging Quality (PI-QUAL) scoring system.^15^ In brief, PI-QUAL is a 5-point Likert scoring system, where 1 indicates no sequences are of diagnostic quality and 5 implies that each sequence individually is of optimal diagnostic quality. The objective criteria used to determine PI-QUAL scores are derived from internationally published minimum standards for MRI conduct.^16^ If necessary, sites will be given recommendations to improve image quality and will be re-evaluated after optimisation for participation in the study.

#### Reporting of MRI

Patients will undergo (or will have undergone) standard of care mpMRI as per their local protocol. The radiologists participating in this trial will be blinded to the DCE sequences and will report the MRI using only the biparametric (T2W and DWI) sequences in report 1. After reporting the bpMRI, the same radiologist will be unblinded to the DCE sequences and will re-report the MRI using the mpMRI sequences (T2W, DWI and DCE) in report 2 (figure 1).

**Figure 1 F1:**
[figure not shown]
The Prostate Imaging Using MRI±Contrast Enhancement trial schema—the approach prior to MRI. *indicates a 1–5 scale of suspicion for the likelihood that clinically significant PCa is present, with 5 representing the greatest score of suspicion. For MRI to be non-suspicious it needs to be scored 1 or 2 on both Likert and PI-RADS V.2.1 systems. For MRI to be suspicious it can be scored 3, 4 or 5 on either Likert or PI-RADS V.2.1 systems. bpMRI, biparametric MRI; DCE, dynamic contrast-enhanced sequence; DRE, digital rectal examination; DWI, diffusion-weighted sequence; mpMRI, multiparametric MRI; PI-RADS, Prostate Imaging Reporting and Data System; PSA, prostate-specific antigen; T2W, T2-weighted sequence.

The MRIs and lesions are scored on a 1–5 scale of suspicion for the likelihood that clinically significant PCa is present, with 5 representing the greatest score of suspicion. Both the traditional Likert and PI-RADS V.2.1 scoring systems will be used to identify any suspicious lesions in the prostate. Suspicious areas (Likert or PI-RADS V.2.1 score ≥3) on either bpMRI or mpMRI will undergo targeted biopsy of the prostate, with cores from contrast-enhanced suspicious areas stored separately.

A summary of the rules for reporting MRI scans in the PRIME trial is listed in box 2. Please see online supplemental appendix 1 for our model reporting proformas, which radiologists participating in the PRIME trial will use to label lesions.

10.1136/bmjopen-2022-070280.supp1Supplementary data

Box 2Summary of MRI reporting rules
**Report 1 (bpMRI: T2W and DWI).**
The radiologist reporting this will be blinded to DCE, with verification of this via an independent person or an automated system (Medical Image Merge (MIM) by MIM Software Inc.).The radiologist should then interpret the bpMRI sequences *blinded* to DCE.Up to four suspicious areas (score ≥3 out of 5 on the Likert or PI-RADS V.2.1 scoring system) can be marked on report 1; if there are more, the four *most suspicious* should only be marked on.The location of the suspicious areas should be labelled according to the PI-RADS V.2.1 41 sector diagram.Once report 1 (bpMRI: T2W and DWI) has been done, this *cannot be altered* after looking at the DCE.
**Report 2 (mpMRI: T2W, DWI and DCE).**
The same radiologist must report both reports 1 and 2.They will then be *unblinded* to the DCE sequence.The radiologist should now complete report 2.The location of the suspicious areas should be similarly labelled according to the PI-RADS V.2.1 41-sector diagram as previously mentioned.On report 2, each of the existing lesions are additionally labelled as one of
**bpMRI positive, mpMRI positive.**
This occurs when a lesion scores 3, 4 or 5 on both bpMRI and mpMRI based on *either* Likert or PI-RADS V.2.1 scoring systems.
**bpMRI positive, mpMRI negative.**
This occurs when a lesion scores 3, 4 or 5 on bpMRI on either Likert or PI-RADS V.2.1 scoring systems, but also scores as 1 or 2 on mpMRI on both Likert and PI-RADS V.2.1 scoring systems.
**bpMRI negative, mpMRI positive.**
There are two instances in which *new targets* may be labelled and drawn onto report 2:
*New* lesions scoring 3, 4 or 5, identified by DCE not previously identified on bpMRI should be marked on as new lesions as *DCE targets* and *bpMRI negative, mpMRI positive*.Lesions that appear *larger* on DCE should be treated as two separate targets.One target depicts the completely overlapping segment from report 1 (bpMRI positive, mpMRI positive).The non-overlapping part which would otherwise not be sampled should be labelled as a *new target* (bpMRI negative, mpMRI positive). This is a subjective decision by the radiologist. A typical example of when to declare this as a separate target is if the non-overlapping part enters an adjacent sector on the PI-RADS V.2.1 sector diagram.A biopsy plan is recommended by the radiologist thereafter for the biopsy operator to follow.

#### Non-suspicious bpMRI and mpMRI

Men whose MRIs do not show suspicious areas on bpMRI and mpMRI (ie, scored 1 or 2 on Likert and PI-RADS V.2.1) will be stratified by PSA density. Men with PSA density of <0.15 ng/mL/mL will not undergo biopsy and men with PSA density of ≥0.15 ng/mL/mL will undergo systematic biopsy.

### Prostate biopsy procedures

#### MRI-targeted biopsy

Men will undergo MRI-targeted biopsy if either their bpMRI or mpMRI identifies a suspicious lesion which scores ≥3 on either Likert or PI-RADS V.2.1. Four targeted cores will be taken per suspicious lesion, and these should be stored and labelled in separate containers to ensure cancer detection from separate suspicious areas is ascertained.

#### Systematic biopsy

Systematic biopsies should be performed after targeted biopsies, with six cores taken from the contralateral side of the MRI lesion, focused on sampling the peripheral zone of the prostate. If there are bilateral MRI lesions or midline lesions, then no systematic biopsies are necessary.

Please see online supplemental appendix 2 for a detailed overview of how our biopsies will be conducted.

10.1136/bmjopen-2022-070280.supp2Supplementary data

#### Prostate histopathology

Both the Gleason score and the Gleason grade group will be reported for the overall biopsy and for each individual target lesion.

#### Pre-trial assessments

For all patients, patient referral would follow clinical suspicion of PCa (eg, raised PSA or abnormal digital rectal examination). To confirm a patient’s eligibility, screening will be undertaken. Patients can enter the trial either before or after they have had their mpMRI scan. If patients are recruited after an mpMRI scan has been carried out, this will only be permitted if the MRI has not been seen by any clinician.

#### Registration procedures

Following consent and confirmation of eligibility, trial processes can commence. The patient will be registered and assigned a trial ID using a central online database (Marvin by XClinical).

#### Intervention procedures

All patients will undergo a full mpMRI scan. This includes T2W, DWI and DCE sequences.

#### Follow-up for results

If bpMRI and mpMRI are non-suspicious and PSA density is <0.15 ng/mL/mL, the patient will be counselled for standard of care follow-up, typically consisting of PSA surveillance. If a decision for prostate biopsy or other tests is made, these results will be recorded after which the participant completes the trial.

#### Multidisciplinary team (MDT) decision making for treatment eligibility

Treatment decisions will be per local standard of care, based on pathology results, and will be recorded. Subsequently, a virtual MDT meeting will be conducted and treatment eligibility decisions blinded to the DCE will be recorded. Once a decision has been recorded, the clinicians will be unblinded to the DCE sequence and the impact that this information makes on treatment eligibility will be evaluated.

#### MRI and pathology quality control

Quality control will be carried out at the end of the study by the PRIME chief radiologists reviewing the original MRIs, who will assess the MRI quality and re-report the MRI blinded to the study reports. Anonymised pathology slides from a proportion of patients may also be reviewed by central pathologists. Any slides assessed outside of the originating site will be returned to the original site after quality control. Quality control results will be reported but will not influence patient management or outcomes.

#### Cost-effectiveness

A within-trial incremental cost-effectiveness analysis will be conducted to calculate the difference in mean cost per diagnosis of clinically significant PCa if a strategy of bpMRI were adopted instead of the current mpMRI standard of care, over a time horizon of 30 days. The difference in cost of avoiding each additional case of clinically insignificant PCa diagnosed may also be calculated.

Costs of procedures will be estimated by applying standard unit costs to resource use data captured within the trial plus other procedures that would be offered to patients in either pathway. Estimates of the resources used (procedures, tests, radiotherapy, chemotherapy, other therapies, surveillance visits and other care events) on the two treatment pathways will be obtained for the theoretical bpMRI cohort using decisions made initially by the MDT with information from the bpMRI scan and any biopsies as a result of that scan, and estimates of the treatment pathway resources used in the theoretical mpMRI cohort will be made subsequently by the MDT on viewing additional information from the mpMRI scan and any further biopsies performed as a result of that scan. This thought experiment is required due to the ethical requirement to use all available information, that is, not just bpMRI and biopsies or just mpMRI and biopsies, when making the actual treatment decision with the patient.

The analysis perspective will be that of the NHS and personal social services. Standard unit costs (eg, NHS reference costs) will be supplemented by unit cost data from the participating trial sites. A microcosting study to provide this information will be undertaken in a small number of sites as part of the trial to investigate the resources employed to deliver bpMRI and mpMRI scans. This information will allow us to understand the MRI booking system, consumption of consumables and staff time as related to delivering bpMRI and mpMRI scans.

Depending on the within-trial cost-effectiveness findings, consideration will be given to extending this analysis using decision analytical modelling to estimate quality-adjusted life-years gained over a lifetime horizon. Quality of life information will be estimated from anonymised patient-level data by the same group from an earlier study in this instance.

### Outcomes

#### Primary outcome

The primary outcome will be the proportion of men with clinically significant PCa detected—any pattern 4 disease on any core (ie, Gleason score ≥3+4 or Gleason grade group ≥2). The time frame for assessment will be when biopsy results are available, at an expected average of 30 days post biopsy.

#### Secondary outcomes

Table 1 lists our secondary outcomes.

**Table 1 T1:** Secondary outcomes in Prostate Imaging Using MRI±Contrast Enhancement

Outcome	Time frame for assessment
Proportion of men with clinically insignificant cancer (Gleason score 3+3/Gleason grade group 1)	When biopsy results are available, at an expected average of 30 days post biopsy
Agreement between bpMRI and mpMRI for score of suspicion	When MRI results are available, at an expected average of 30 days post MRI
Proportion of bpMRI scans and mpMRI whose quality was deemed adequate for reporting	When MRI results are available, at an expected average of 30 days post MRI
Agreement between bpMRI and mpMRI for radiological staging decision	When MRI results are available, at an expected average of 30 days post MRI
Agreement between bpMRI and mpMRI for treatment eligibility	When treatment eligibility is discussed in a multidisciplinary meeting, at an expected average of 30 days post biopsy
Test performance characteristics for bpMRI and mpMRI when using the Likert scoring system in comparison to the PI-RADS scoring system	When biopsy results are available, at an expected average of 30 days post MRI
Proportion of men with clinically significant cancer missed by bpMRI-targeted and mpMRI-targeted biopsies and detected by systematic biopsy	When biopsy results are available, at an expected average of 30 days post biopsy
Cost-effectiveness of bpMRI compared with mpMRI (cost per diagnosis of prostate cancer)	At an expected average of 30 days post intervention

bpMRI, biparametric MRI; mpMRI, multiparametric MRI; PI-RADS, Prostate Imaging Reporting and Data System.

### Sample size

The margin of clinical unimportance to allow a conclusion of non-inferiority of bpMRI to mpMRI to be made was set at 5 percentage points; that is, if the lower bound of the 95% CIs for the difference in detection rates of bpMRI-targeted biopsy compared with mpMRI-targeted biopsy is above −5 percentage points, then bpMRI will be deemed as non-inferior.

Using simulation, we used an mpMRI underlying probability of detecting clinically significant cancer of 38%^3^ and the following two key probabilities to determine the sample size:

The probability that a patient found to have no suspicious lesions on bpMRI or have no clinically significant PCa on bpMRI-targeted biopsy will have clinically significant PCa on mpMRI-targeted biopsy.The probability that a patient found to have no suspicious lesions on mpMRI or have no clinically significant PCa on mpMRI-targeted biopsy will have clinically significant PCa on bpMRI-targeted biopsy.

Assuming the probability of A is greater than the probability of B, and applying McNemar’s test in each of 1000 simulation runs for each combination of probabilities A and B ranging from 0 to 0.05, a sample size of 400 patients gives more than 90% power across these probabilities of A and B. Accounting for 20% dropout or exclusion after enrolment, the study will require at least 500 patients.

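### With A and B defined as printed, 400 men do not give more than 90% power for every A > B up to 0.05; exact power at A=0.05, B=0 is about 34–57%

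*Protocol article*

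**What the plan says.** The Sample size section of the protocol article gives every input needed to check its power claim.

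- **Margin and success rule.** The margin for "non-inferiority of bpMRI to mpMRI to be made was set at 5 percentage points". Success is judged on "the lower bound of the 95% CIs for the difference in detection rates of bpMRI-targeted biopsy compared with mpMRI-targeted biopsy", which must lie above −5 points.
- **mpMRI detection rate.** 38%.
- **A.** The probability that a man "found to have no suspicious lesions on bpMRI or have no clinically significant PCa on bpMRI-targeted biopsy will have clinically significant PCa on mpMRI-targeted biopsy". It is therefore conditional on a negative bpMRI result.
- **B.** The mirror image: the probability that a man "found to have no suspicious lesions on mpMRI or have no clinically significant PCa on mpMRI-targeted biopsy will have clinically significant PCa on bpMRI-targeted biopsy".
- **Scope.** A is taken to exceed B, and McNemar's test is applied in 1000 simulated trials "for each combination of probabilities A and B ranging from 0 to 0.05".
- **Claim.** "a sample size of 400 patients gives more than 90% power across these probabilities of A and B". Allowing for 20% dropout, 400 becomes 500.

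**The concern.** A power statement covering every combination has to hold at the least favourable one, which is A=0.05 with B=0. There the printed definitions imply a true deficit of more than 3 points against a 5-point margin. The remaining gap is only about two standard errors with 400 men, so power near 50% is to be expected, not 90%.

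The simulated test adds to the doubt. An ordinary McNemar's test compares the two detection rates against equality. It does not test whether the difference lies above −5 points, so the simulation as described is not a simulation of the stated success rule.

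This sentence is the only justification given for the sample size. The shortfall falls where contrast adds most to detection. In that region a true deficit inside the margin could often fail to show non-inferiority, and a reader told that this risk is below 10% might take such a failure as evidence that contrast is needed.

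**Working it through.** **Inputs** (all from the Sample size section): n = 400 evaluable men, mpMRI detection 0.38, margin −0.05, two-sided 95% interval, and A > B in 0 to 0.05. The interval method is not named, so two are shown: Wald and Tango score.

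**Dropout step.** 400/(1 − 0.20) = 500. This reproduces.

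**Cell probabilities under the printed definitions.** Let x be the probability that bpMRI does not detect significant cancer.

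- Detected by mpMRI only: p10 = A·x
- Detected by bpMRI only: p01 = 0.62·B
- Detected by neither: 0.62(1 − B) = x(1 − A), so x = 0.62(1 − B)/(1 − A)
- Difference, bpMRI minus mpMRI: p01 − p10 = −0.62(A − B)/(1 − A)

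**Worst corner, A=0.05, B=0.**

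- p10 = 0.62 × 0.05/0.95 = 0.0326 and p01 = 0, so the difference is −3.26 points.
- Distance to the margin: 5 − 3.26 = 1.74 points.
- SE = √[(0.0326 − 0.0326²)/400] = 0.89 points.
- Normal approximation: Φ(0.01737/0.00888 − 1.96) ≈ 0.50.
- Exact: with B=0 the only discordant men are those detected by mpMRI only, expected 400 × 0.0326 ≈ 13. The Wald lower limit stays above −5 points with up to 13 such men (at 13 it is −4.99, at 14 it is −5.30). The score limit does so with up to 11. The binomial probabilities are 56.7% (Wald) and 34.4% (score).
- If all 500 men were evaluable, the same corner would reach 63% (Wald) or 43% (score).

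**Exact power elsewhere, n=400** (enumeration of both discordant cells):

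| A | B | Wald | Score |
|---|---|---|---|
| 0.05 | 0 | 56.7% | 34.4% |
| 0.05 | 0.01 | 68.4% | 54.0% |
| 0.05 | 0.02 | 81.1% | 71.1% |
| 0.05 | 0.03 | 89.9% | 84.0% |
| 0.05 | 0.04 | 95.0% | 92.0% |
| 0.04 | 0 | 84.2% | 65.9% |
| 0.04 | 0.01 | 90.2% | 81.3% |
| 0.04 | 0.02 | 95.3% | 90.7% |
| 0.03 | 0 | 97.6% | 91.2% |

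On a grid with steps of 0.005 and A > B there are 55 combinations. Of these, 14 (Wald) or 20 (score) are below 90%, so 75% or 64% meet the claim.

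**Other readings, at A=0.05, B=0.**

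- A and B as joint probabilities: the true difference is exactly −5 points, and power is 2–6%.
- Success taken as a non-significant McNemar's test: 0.1%.
- A as the share of mpMRI-detected cancers missed by bpMRI: p10 = 0.38 × 0.05 = 0.019, and power is 97.7% (Wald) or 91.7% (score). This is the worst of the 55 combinations, and all of them exceed 90%.

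**Men needed for 90% at the corner.** The normal formula gives (1.96 + 1.2816)² × 0.03157/0.01737² ≈ 1,100, but exact power at 1,100 is only 86.8% (Wald) or 78.6% (score). Exact enumeration in steps of 25 gives about 1,250 (Wald) to 1,400 (score).

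**The case against.** The strongest reply is that the power may be right and the definition of A wrong. The simulation fixes mpMRI detection at 38%. A natural way to program it is to draw the mpMRI result first, let bpMRI miss a fraction A of the cancers mpMRI finds, and let it find a fraction B among the mpMRI-negatives. That reading gives more than 90% for every combination under both interval methods, which matches the published sentence. This stands as a real possibility, so a reader should not infer that no reading supports the figure. It does not rescue the text as printed, which conditions A on a negative bpMRI result.

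A second reply is that power averaged over the 0.005 grid is 92.7% with the Wald interval. With the score interval it is 87.5%, and in any case the claim is made for each combination, not for an average.

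Third, A=0.05 with B=0 is the extreme point of the range, and the low end of 34% depends on choosing a score interval. Both are true. The choice of interval may properly be left to the analysis plan. But the Wald interval also misses 90% at 14 combinations, so the finding does not depend on that choice.

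Finally, low power here raises the chance of missing true non-inferiority. It does not raise the chance of declaring non-inferiority falsely.

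**Conclusion.** As written, the power statement is wrong. Under the printed definitions, 38% mpMRI detection and the stated confidence-interval rule, 400 men give about 34–57% power at A=0.05, B=0, and a quarter to just over a third of the grid is below 90%. The result assumes a two-sided 95% interval and 400 evaluable men; the range reflects the unnamed interval method.

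A reader might infer that the trial is underpowered or needs more men. The document does not support that. For most of the range the claim is met, and with B=0 it holds for A up to about 0.030 (score) or 0.037 (Wald). If A was simulated as a miss rate among mpMRI-detected cancers, it is met everywhere. What is established is narrower: the printed definition of A, the simulated test and the power figure cannot all be correct together.

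**What to change.** First check in the simulation code how A was parameterised and what counted as success in each run.

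- **If A was a miss rate among mpMRI-detected cancers:** correct the printed definition of A, and state that success was the confidence-interval rule if that is what was simulated. If it was not, rerun with that rule.
- **If A was as printed:** rerun with the rule that the lower 95% limit of the paired difference exceeds −5 points, name the interval method, tabulate power by (A, B), and restate the claim. Possible wording with the score interval: 400 evaluable men give at least 90% power for A up to about 0.030 if B=0, 0.035 if B=0.01 and 0.040 if B=0.02; at A=0.05, B=0 power falls to about 34% (57% with a Wald interval). Exact score power at those three limits is 91.2%, 90.8% and 90.7%.

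The cost is a look at the code, possibly a short rerun, and one or two reworded sentences. The sample size, margin and success rule stay as they are. The 1,250 to 1,400 men needed for 90% at the corner are given for information only and are not a request to enlarge the trial.
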